**Fig. 1 Fig1:**
[figure not shown]
Flowchart of study trial. Study interventions in blue and regular care in yellow, in red the reference cohort. * The intake of red triaged participants will be assessed, and individuals will be contacted via phone or scheduled for an appointment at the outpatient clinic for counselling

### Study setting: Dutch CRC screening program

In the Netherlands, a national CRC screening program was gradually implemented in 2014, using biennial FIT. All individuals between the age of 55 and 75 years old receive an information leaflet with information on CRC, FIT, advantages and disadvantages of CRC screening enclosed with a FIT. Participation and returning FIT is free of charge. In case of a positive FIT, colonoscopy is recommended. FIT positive participants receive, by mail, the result of their stool test together with an invitation for a pre-colonoscopy consultation at the outpatient clinic of a certified endoscopy centre. Once both the medical professional and the patient have agreed to proceed with screening colonoscopy, detailed information on bowel preparation is provided during the pre-colonoscopy consultation, and colonoscopy is scheduled within a three-week timeframe. Reasons not to schedule screening colonoscopy are a life expectancy of less than five years and FIT positive individuals who are unable or unwilling to undergo colonoscopy [11]. Each year around 2.2 million individuals are invited to participate in the national CRC screening program, approximately 70% return their FIT of which 4–5% have a positive FIT. As a consequence, approximately 70.000 participants are referred to the outpatient clinic annually [12].

### Sample selection

All FIT-positive participants of the Dutch CRC screening program are eligible for inclusion if they are able to provide informed consent. Patients are excluded when having 1) a visual disability 2) lack of internet access or do not have a relative with internet access 3) Dutch illiteracy. FIT-positives are requested to contact the outpatient clinic of the endoscopy centre they have been referred to, prior to their scheduled face-to-face consultation. Patients will be recruited during this phone contact. If they choose to have a face-to-face visit instead of the DIT intervention, they will not be included in the study.

### Intervention

All enrolled participants will receive the DIT instead of a counselling visit. The DIT is a web-based platform with 3D animation videos guided by a voiceover and a medical questionnaire. The patient education in the DIT was developed in collaboration with Informed. B.V., which is a company specialized in developing animation tools to inform patients, including low literacy, about medical procedures. To ensure that the information provided met the national requirements, the Dutch National Institute for Public Health and Environment (RIVM) as well as the Dutch screening organization were consulted. The animation videos provide information about the positive FIT result, CRC risk and colonoscopy procedure, including information about the complication risks and sedation. For a preview of the animation videos, scan the QR-code shown in Fig. 2. Once participants complete the DIT, a risk assessment will be conducted, categorizing participants’ intake result as “green” in case no further action is required or “red” if action is necessary. In case the latter, a gastroenterology nurse or gastroenterologist will evaluate the participant on paper before proceeding with colonoscopy, and determine if an outpatient consultation is necessary for further evaluation. All participants will be contacted by phone to schedule the colonoscopy, and personalized animated bowel preparation instructions will be send via the DIT.

**Fig. 2 Fig2:**
[figure not shown]
QR code to animation video. To access a preview of the animation videos used in the DIT, scan the QR code

### Patient and public involvement

Study inclusion has been ongoing since October 2021 and has an anticipated end date of March 2024. The first ten included participants who used the DIT were interviewed to evaluate its usability. No technical issues were identified, only minor modifications were suggested, such as rephrasing certain questions of the medical questionnaire and a navigation tool to allow for easy movement between the pages. Moreover, gastroenterologists and gastroenterology nurses were involved in the first evaluation of the DIT and asked to provide feedback. The provided feedback from a patient and healthcare perspective regarding usability of the DIT was evaluated and implemented for future users.

### Sample size calculation

A sample size calculation was performed for demonstrating non-inferiority of the DIT versus all participants visiting the outpatient clinic with regard to the primary endpoint; adequate bowel preparation, defined as a Boston Bowel Preparation Score (BBPS) of 6 or higher. The choice of non-inferiority design was motivated by the expectation that the DIT will improve secondary outcomes regarding costs and satisfaction. According to the Dutch national CRC screening organization at least 90% of all participants in the CRC screening program must have a BBPS of at least 6. Based on earlier data, currently in 97.5% a BBPS of 6 or higher is achieved among participants of the Dutch screening program. With a clinically acceptable difference of -0.5%, corresponding to at least 89.5% of participants achieving adequate bowel preparation, the non-inferiority margin is set at -8.0%. To achieve 90% power with a one-sided Exact test at a 2.5. significance level, 738 participants are needed. Anticipating 30% loss to follow-up or withdrawal of participants, we aim to include 1000 participants.

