### Study design

This is a prospective, multicentre cohort study with a non-inferiority design to assess the effectiveness of a pre-colonoscopy eHealth tool in participants of a FIT-based CRC screening program. Study sites are located in the Netherlands, and include an academic hospital, regional hospitals, and endoscopy centres. In this single-arm study, all enrolled participants will receive the DIT intervention instead of standard counselling at the outpatient clinic. For analyses of our primary outcome, we will compare colonoscopy data of the study participants with that of 1000 FIT positive participants who received pre-colonoscopy counselling at the outpatient clinic of endoscopy centres that did not participate in the DIT-trial (Fig. 1). Additionally, we will assess patient-related outcome measures, including anxiety levels, satisfaction and knowledge transfer among a reference cohort consisting of 100 FIT-positive participants who received pre-colonoscopy counselling at the outpatient clinic. This study was designed according to the Standard Protocol Items: Recommendations for Interventional Trials (SPIRIT) 2013 shown in Supplementary Table 1.

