### Statistical analysis

Continuous data will be summarized using means and standard deviations, or medians and interquartile ranges in case of skewed distributions. Categorical data will be presented in relative frequencies and counts. Comparison of normally distributed continuous variables will be done with the Student t-test or Mann-Whitney U test in case of skewed distributions. Categorical outcomes will be analysed using χ2 test. Non-inferiority of our primary outcome will be evaluated by whether the lower bound of the two sided 95% confidence interval of the observed difference in adequate bowel preparation rate is above the non-inferiority margin of 0.5%.

For repeated measurements within participants, e.g. the total STAI-6 score before and after the DIT, paired tests will be used to analyse differences. Differences are considered significant in case *p* ≤ 0.05. Other secondary outcome parameters will only be obtained from study participants who underwent the DIT intervention, these results will be reported using descriptive statistics.

Statistical analysis will be performed using IBM SPSS statistics.

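### The -8.0% margin secures the stated 89.5% floor only if the comparator cohort reaches 97.5%, because the decision rule contains no absolute criterion

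*Protocol article*

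**What the plan says.** All references are to the protocol article.

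- **Sample size calculation** gives the programme requirement, "at least 90% of all participants in the CRC screening program must have a BBPS of at least 6", and the current level, "currently in 97.5% a BBPS of 6 or higher is achieved among participants of the Dutch screening program".
- The same section defines the tolerance, "With a clinically acceptable difference of -0.5%, corresponding to at least 89.5% of participants achieving adequate bowel preparation", and then fixes the margin on the difference scale: "the non-inferiority margin is set at -8.0" percent.
- **Study design** names the comparison: "we will compare colonoscopy data of the study participants with that of 1000 FIT positive participants". These people were counselled face to face at centres outside the trial.
- **Statistical analysis** judges non-inferiority by the "lower bound of the two sided 95% confidence interval of the observed difference in adequate bowel preparation rate". The margin printed there is 0.5%, not -8.0%.

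No section of the article makes success depend on the DIT group's own rate.

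**The concern.** The tolerance and the test use different reference points. The 0.5-point tolerance is taken from a fixed standard (90%). The test measures a difference from a cohort whose rate is still to be observed. The 97.5% that links the two is a planning figure, and the decision rule does not hold the comparator to it.

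If the cohort falls below 97.5%, the rate that the margin excludes falls with it, point for point. A non-inferiority claim would then no longer carry the assurance of at least 89.5% that the article attaches to it. That assurance matters to anyone deciding whether the consultation can be replaced, because the national requirement is itself an absolute rate.

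**Working it through.** **Inputs from the article.** National minimum 90%; tolerance 0.5 points; current rate 97.5%; margin -8.0 points; two-sided 95% confidence interval; 1000 comparators; 1000 DIT participants enrolled; 738 needed; 30% loss, so 1000 × (1 - 0.30) = 700 evaluable. DIT group sizes of 700, 738 and 1000 are therefore used.

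**Assumptions.** Comparator rates of 96% and 95% are not in the article; they show the range. The interval for the difference is taken as Wald and the interval for a single rate as exact (Clopper-Pearson), since the article names neither.

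**Step 1. The article's own figure.** 90 - 0.5 = 89.5 and 97.5 - 8.0 = 89.5. The two agree, but only because 97.5 is put in for the comparator. In general the excluded rate is (comparator rate - 8.0): 88.0% at 96% and 87.0% at 95%.

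**Step 2. What passes.** With DIT rate pD on nD participants and comparator rate pC on 1000, non-inferiority is declared if

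pD - pC - 1.96 × √[pD(1 - pD)/nD + pC(1 - pC)/1000] > -0.08.

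- 643/700 (0.9186) against 0.975: -0.0564 - 1.96 × 0.01146 = -0.0789, which passes.
- 628/700 (0.8971) against 0.95: -0.0529 - 1.96 × 0.01339 = -0.0791, which passes.

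**Step 3. How often a true 89.5% passes.** The probabilities of all pairs of binomial counts that satisfy the rule are summed, with the true DIT rate at 89.5%.

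| True comparator rate | Rate the margin excludes | Smallest passing DIT count if that rate is observed (700 / 738 / 1000) | Chance that a true 89.5% passes (700 / 738 / 1000) |
|---|---|---|---|
| 97.5% (article) | 89.5% | 643 (91.9%) / 677 (91.7%) / 915 (91.5%) | 3% / 3% / 3% |
| 96% (assumed) | 88.0% | 634 (90.6%) / 668 (90.5%) / 903 (90.3%) | 22% / 23% / 26% |
| 95% (assumed) | 87.0% | 628 (89.7%) / 662 (89.7%) / 894 (89.4%) | 46% / 48% / 56% |

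**Step 4. How likely a low comparator is by chance.** If the true rate is 97.5%, the standard error with 1000 people is √(0.975 × 0.025/1000) = 0.5 points. An observed 95.4% or lower, roughly where an observed DIT rate below 90% starts to pass with 738 participants, has probability about 0.00008. A lower comparator would have to reflect a real difference between centres.

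**Step 5. An absolute condition.** The smallest count whose exact two-sided 95% lower bound exceeds the limit, and the binomial power at n = 700:

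| Limit | Count needed (700 / 738 / 1000) | Power at true 93% | 94% | 95% |
|---|---|---|---|---|
| 89.5% | 643 / 677 / 915 | 89% | 99% | about 100% |
| 90% | 646 / 681 / 919 | 79% | 97% | 99.9% |

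The 89.5% counts equal those the difference rule already needs against an observed 97.5%. With this condition added, a true 89.5% succeeds at most 2.5% of the time whatever the comparator rate.

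**Step 6. The other printed margin.** If the 0.5% in the analysis section is read as -0.5% and governs, a DIT group of 738 would need 726/738 (98.4%) against an observed 97.5%. The concern then largely disappears, but power with both true rates at 97.5% is only about 11%.

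**The case against.** The strongest reply is that the plan works as intended under its own assumption. At 97.5% the rule already demands an observed DIT rate above 91%, and a true rate of 90.0% would pass only about 7% of the time. The article cites earlier programme data for 97.5% and gives no reason to expect other centres in the same programme to run lower. This stands, and it limits the size of the point.

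Two further replies also stand. No fixed difference margin fixes an absolute rate, and the article openly accepts half a point below the national minimum as a clinical judgement. The DIT rate will be reported in any case, so a shortfall would be visible. They do not answer the point itself: the article says that its margin corresponds to an absolute floor, and the rule it describes secures that floor at one planning value only.

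A reader might go further and infer that the margin is simply too wide and should be about 2.5 to 3 points. The article does not support that. Such a figure comes from what the sample can power, not from a clinical argument, and true DIT rates of 93-94%, which an 8-point margin would usually pass, meet the 90% minimum.

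**Conclusion.** The point holds in limited form. The floor of at least 89.5% depends on a comparator rate of 97.5% or higher, which the decision rule does not require. The consequence is small at 97.5% (about a 3% chance that a true 89.5% passes) and large if the comparator is lower: 22-26% at 96% and 46-56% at 95%. Those two rates are assumptions.

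A reader might infer that the trial as planned is likely to endorse a tool that breaches the national minimum, or that a non-inferiority result would lead automatically to national replacement. The article supports neither: the first needs a comparator well below the stated rate, and no automatic adoption is described.

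All of this is conditional on -8.0% being the operative margin. The sample size and analysis sections disagree on that and must be reconciled first. A statistical analysis plan, not shown, may contain an absolute criterion; the correspondence as printed would still need correcting.

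**What to change.** 1. Reconcile the margin between the sample size and statistical analysis sections.
2. State that 89.5% follows from -8.0 points only at a comparator rate of 97.5% or higher.
3. Keep the difference test and add a second condition for success: the lower bound of the two-sided 95% confidence interval of the DIT group's own adequate-preparation rate exceeds 89.5%, the article's own floor (643/700, 677/738 or 915/1000).
4. Report that rate with its interval against the 90% national minimum; excluding 90% would need 646/700, 681/738 or 919/1000.

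The cost is one added criterion. No extra participants or data are needed, because the bowel preparation scores are already retrieved from the national database. Both conditions must be met, so no multiplicity adjustment is needed. The chance of success falls only if the tool performs near the minimum: with 700 evaluable participants, power for the added condition is still 89% at a true rate of 93%.

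### If the -8.0-point margin is kept, it protects the plan's own 89.5% floor only when the comparator rate is 97.5% or higher, and nothing else in the decision rule checks that floor

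*Protocol article*

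**What the plan says.** Under Sample size calculation, the protocol article gives a national requirement that "at least 90% of all participants in the CRC screening program must have a BBPS of at least 6" and reports that "currently in 97.5% a BBPS of 6 or higher is achieved among participants of the Dutch screening program". It then sets a tolerance of -0.5 points from the national requirement and not from current performance, "corresponding to at least 89.5% of participants achieving adequate bowel preparation, the non-inferiority margin is set at -8.0" percent.

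Under Study design, the comparator is not a fixed rate. It is "1000 FIT positive participants who received pre-colonoscopy counselling at the outpatient clinic of endoscopy centres that did not participate in the DIT-trial". Data collection confirms that their colonoscopy data will be retrieved for the primary comparison.

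Under Statistical analysis, the decision rests on "the lower bound of the two sided 95% confidence interval of the observed difference in adequate bowel preparation rate". The same sentence prints a different margin, without a sign: it asks whether the "difference in adequate bowel preparation rate is above the non-inferiority margin of 0.5" percent.

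The article does not test the DIT group's own rate against 89.5%, and it does not say what follows if the comparator is not at 97.5%.

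**The concern.** The clinical criterion is absolute: at least 89.5% of participants adequately prepared. The decision rule is relative: a difference from whatever the comparator centres show. The two coincide at one comparator rate only. If the comparator does worse than 97.5%, a margin of -8.0 points moves the lowest acceptable DIT rate below 89.5%, and so below the 90% national requirement as well.

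At stake is what a positive result would mean. A reader of the sample size section would take non-inferiority to imply a DIT rate of at least 89.5%, with a 2.5% one-sided error. Under a -8.0 difference rule, the error against that floor depends on how well a non-random set of other centres performs.

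**Working it through.** **Inputs.** From Sample size calculation: national requirement 90%, tolerance 0.5 points, current rate 97.5%, margin -8.0 points, one-sided 2.5%, target 1000 with 30% loss. From Study design: 1000 comparators. From Statistical analysis: two-sided 95% confidence interval for the difference. Assumed: 1000 × 0.70 = 700 evaluable DIT participants. The article does not name the interval method, so Wald and Newcombe limits are both shown.

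**1. The plan's margin reproduces.** 90 - 0.5 = 89.5, and 89.5 - 97.5 = -8.0.

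**2. The floor that -8.0 implies.** Implied floor = comparator rate - 8.0.

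| Comparator rate | Implied DIT floor |
|---|---|
| 99% | 91% |
| 98% | 90% |
| 97.5% | 89.5% |
| 97% | 89% |
| 96% | 88% |
| 95% | 87% |

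**3. Chance of passing when the DIT is truly at 89.5%.** Both binomials were enumerated in full (DIT n = 700, comparator n = 1000). The probability was summed over every pair of counts whose lower 95% limit for the difference exceeds -0.08. The Wald limit is d - 1.96 × √[p₁(1-p₁)/n₁ + p₂(1-p₂)/n₂].

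| True comparator rate | P(declare non-inferior), Newcombe to Wald |
|---|---|
| 98% | about 1% |
| 97.5% | 2.4-3.1% |
| 97% | 5.5-6.9% |
| 96.5% | 11-13% |
| 96% | 19-22% |
| 95% | 43-46% |

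More DIT data does not help. Over DIT sizes of 700 to 1000, the range is 19-26% at 96% and 43-56% at 95%.

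**4. Smallest passing DIT count (Wald, n = 700).**
- Observed comparator 975/1000: 643/700 (91.9%). Check: d = 0.9186 - 0.975 = -0.0564; SE = √(0.9186 × 0.0814/700 + 0.975 × 0.025/1000) = 0.01146; lower limit = -0.0564 - 0.0225 = -0.0789, which passes.
- Observed comparator 950/1000: 628/700 (89.7%). Check: d = -0.0529; SE = 0.0134; lower limit = -0.0791, which passes. With Newcombe limits 629/700 is needed.
- Observed comparator 940/1000: 622/700 (88.9%).

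An observed DIT rate under 89.5% therefore passes only if the observed comparator is about 95% or lower.

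**5. The margin printed in the analysis section.** Read as -0.5 points, a DIT rate under 89.5% lies within the margin only if the comparator is below 90%, because 90 - 0.5 = 89.5. At comparator rates of 94-97.5%, a DIT truly at 89.5% passes with probability below 0.000001. The problem in step 3 therefore comes from -8.0 and not from 0.5.

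**6. Adding a floor condition.** The exact two-sided 95% lower limit for the DIT rate first exceeds 89.5% at 643/700. With both conditions required, a DIT truly at 89.5% passes with probability about 2.1% or less at every comparator rate checked (94-98.5%). The binomial tail gives the chance of meeting the floor condition:

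| True DIT rate | P(at least 643/700) |
|---|---|
| 97.5% | about 1.000 |
| 95% | 0.9998 |
| 94% | 0.991 |
| 93% | 0.894 |
| 92% | 0.590 |

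**The case against.** Five things can be said against the point.

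- **The printed rule does not use -8.0.** This stands. A reader might infer that the rule in the analysis section already lets through a DIT below the floor. It does not, because that section prints 0.5%. The contradiction between the sections comes first, and this point depends on how it is resolved. It does not go away, though: carrying -8.0 across from the sample size section would repair the contradiction and bring in this problem. Keeping -0.5 would need 20,490 per arm with 97.5% in both groups, far beyond the planned 1000.
- **The large probabilities need a poor comparator.** This stands. The article says 97.5% is current in the same national programme. At a true 97.5%, observing 950 or fewer of 1000 has probability about 0.000005. A reader might infer that the comparator is expected to fall short; no section gives evidence of that.
- **The 628/700 case is not a breach.** This stands. At 89.7% it is above the 89.5% floor as an observed rate and below only the 90% requirement, from which the plan expressly tolerates 0.5 points.
- **Any fixed difference margin has a floor that moves with the control rate.** True in general, and the stated aim is a comparison with outpatient care. What is particular here is that the margin is justified solely by an absolute floor. The article does not say that 89.5% was meant as a pass/fail criterion, so that cannot be assumed either.
- **A second condition costs power.** This stands near the floor. With a 95% comparator (Wald), power falls from 0.998 to 0.894 at a true DIT rate of 93%, and from 0.975 to 0.590 at 92%.

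**Conclusion.** The point holds conditionally. If -8.0 is the margin kept, the difference rule protects the 89.5% floor only when the comparator rate is 97.5% or higher. Below that, the error against the floor exceeds the nominal 2.5%: modestly for a half-point shortfall (5.5-6.9%) and seriously at 1.5 points or more (19-22% at 96%, 43-46% at 95%). Above 97.5% the rule is stricter than the floor, so the weakness runs in one direction only.

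The figures assume 700 evaluable DIT participants, 1000 comparators, a true DIT rate of 89.5% and Wald or Newcombe limits. The comparator range is an assumption, not a forecast. The point is worth acting on because the remedy is cheap and enforces a standard that the plan itself states. It does not show that the study will reach a wrong conclusion.

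**What to change.** First reconcile the margin between Sample size calculation and Statistical analysis, and state its sign.

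If -8.0 points is kept, add to Statistical analysis: *Non-inferiority will be concluded only if (a) the lower limit of the two-sided 95% confidence interval for the difference exceeds -8.0 percentage points and (b) the lower limit of the exact two-sided 95% confidence interval for the adequate-preparation rate in the DIT group exceeds 89.5%.* With 700 evaluable participants, (b) means at least 643 adequately prepared.

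Cost: no extra patients and no new data, since the bowel preparation scores are already to be retrieved. Power is essentially unaffected at a true DIT rate of 95% or more, but it falls when the DIT is close to the floor: condition (b) is met with probability 0.894 at 93% and 0.590 at 92%. The article says inclusion has been running since October 2021 in a single-arm study, so this changes the primary decision rule during recruitment. It must be documented as such, with its date and reason.

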**Methods:**

This is a prospective multicentre single-arm, non-randomized study with a non-inferiority design. The DIT will triage a total of 1000 participants and inform them about CRC risk, colonoscopy, sedation, and provide bowel preparation instructions. Participants identified as high-risk (i.e., red-triaged) will be contacted by phone or scheduled for an appointment at the outpatient clinic. The primary outcome measure will be adequate bowel preparation rate, defined as the proportion of participants with a Boston Bowel Preparation (BBPS) score ≥ 6. To compare our primary outcome, we will use colonoscopy data from 1000 FIT positive participants who visited the outpatient clinic for pre-colonoscopy consultation. Secondary outcomes will include participation rate, colonoscopy adherence rate, patient experience in terms of satisfaction and anxiety, knowledge transfer, number of outpatient visits that can be averted by the DIT, and cost-effectiveness of the tool. Ethical approval was obtained from the Medical Ethical Committee of the Erasmus Medical Center (MEC-2021-0098).

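### The enrolment target of 1000 does not follow from 738 evaluable participants and 30% loss: 30% requires 1055, and 1000 covers at most 26.2%

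*Protocol article*

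**What the plan says.** The protocol article, under Sample size calculation, gives the requirement as follows: "To achieve 90% power with a one-sided Exact test at a 2.5. significance level, 738 participants are needed". The next sentence sets the recruitment target: "Anticipating 30% loss to follow-up or withdrawal of participants, we aim to include 1000 participants".

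The Methods part of the abstract shows that this target is for the intervention group alone: "The DIT will triage a total of 1000 participants". The 1000 comparison participants are a separate set, whose colonoscopy data are retrieved from the screening database (Study design; Data collection). The article gives no other attrition figure and no other inflation rule.

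**The concern.** The step from 738 to 1000 is the only justification the article offers for its enrolment target, and it tells the reader how much loss the trial can bear. The text implies 30%. If 1000 does not cover 30%, a trial that loses exactly what it expected to lose still falls below the number it says it needs. A reader of the primary result would then be working from a wrong tolerance. What is at stake is the accuracy of a stated design figure. Whether power also suffers is a separate question, checked below.

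**Working it through.** **Inputs**, all from the protocol article, Sample size calculation, unless noted:

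- required participants: 738
- anticipated loss or withdrawal: 30%
- enrolment target: 1000 (also in the abstract, Methods)
- current rate of adequate preparation: 97.5%
- lowest acceptable rate: 89.5%
- exact one-sided test, 90% power, level printed as 2.5 and read here as 2.5%

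**Step 1. Can 1000 be reproduced from 738 and 30%?**

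- Standard inflation, n/(1 - d): 738/(1 - 0.30) = 1054.3, rounded up to 1055. Check: 1055 x 0.70 = 738.5, which meets 738.
- The common but mistaken rule, n x (1 + d): 738 x 1.30 = 959.4, rounded up to 960. At 30% loss that leaves 960 x 0.70 = 672.

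Neither rule gives 1000. It is 55 below the first result and 40 above the second.

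**Step 2. What does 1000 deliver?**

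- Evaluable at 30% loss: 1000 x 0.70 = 700.
- Shortfall: 738 - 700 = 38, and 38/738 = 5.1%.
- Largest loss that still leaves 738: 1 - 738/1000 = 26.2%.

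**Step 3. What does the shortfall do to power?** This depends on how 738 was obtained, and the article's stated rates do not yield it. An exact one-sample test of 97.5% against 89.5% reaches 90% power with about 95 participants. Power at 700 therefore has to be given under several readings:

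| Reading | Power at 700 |
|---|---|
| The article's own rates: exact one-sample test, 89.5% against 97.5% | over 99.9% |
| Exact one-sample test, 89.5% against an assumed 93% | 89.4% (critical count 643, attained level 0.0214) |
| 738 taken to give exactly 90%, scaled by the normal approximation: Φ((1.960 + 1.282) x √(700/738) - 1.960) | about 88.4% |

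The 93% in the second row is an assumption and does not appear in the article. It is shown because it matches 738: under it, power stays at or above 90% from n = 738 onwards (89.9% at 737, 91.9% at 738). Exact power moves in a sawtooth, however. Under the same assumption it first reaches 90% at n = 695 (90.4%), is 89.4% at 700 and is 90.7% at 706. So 700 lies in the range where power hovers around 90%.

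**Step 4. Is another origin of 738 possible?** A two-group calculation comes close, with a 90% control rate, a true rate of 89.5% and an 8% margin. The distance to the margin is 0.08 - 0.005 = 0.075. Per group, (0.90 x 0.10 + 0.895 x 0.105) x (1.960 + 1.282)²/0.075² = 343.7, or 369.8 with continuity correction, for a total of 739.7. The article does not state this reading. Under it the intervention group alone would need about 370, and 700 would be ample.

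**The case against.** The strongest counter-argument is that this is a round recruitment aim set against a loss rate that is only anticipated. The gap is 30% against 26.2%, or 3.8 percentage points, and no estimand, analysis or conclusion depends on it. This stands as an argument about weight, and it is why the point is minor. It does not make the sentence correct: rounding to allow for loss should go up, and 1000 is 55 below what 30% requires.

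A reader might infer that the trial is underpowered at 700. The documents do not support that. The 89.4% figure rests on a 93% rate that the article never gives, and even then 90% is first reached at 695. With the article's own 97.5% against 89.5%, power at 700 exceeds 99.9%. Nor can 89.5% against 93% be called the only design behind 738, since a two-group total of about 740 is also close.

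A reader might also take the abstract's 1000 as a second instance of the error. It only repeats the target, with no loss rate and no required number. Its use here is to show that the 1000 are users of the digital tool and not the total of both groups.

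Finally, 738 itself and the margin are the larger open questions. The sample size section says "the non-inferiority margin is set at -8.0"%, while the statistical analysis section uses 0.5%. With a 0.5% margin and 97.5% in both groups, about 20,490 per group would be needed, and neither 738 nor 1055 would be relevant. That is true, but it is a separate matter. Settling it would not make 70% of 1000 equal 738.

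**Conclusion.** The enrolment sentence is wrong as written. With 738 needed and 30% loss, the target is 1055. The target of 1000 leaves 700 evaluable, 38 (5.1%) short, and covers at most 26.2% loss. This rests only on three printed numbers and on reading the 1000 as intervention participants, which the abstract confirms.

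The consequence for power is small or nil, and its size depends on assumptions: from about 88.4% if 738 is taken to give exactly 90%, through 89.4% under the assumed 93%, to over 99.9% on the article's stated rates. It is a minor correction of a stated figure. It is not evidence that more participants are needed.

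**What to change.** Keep the target of 1000 and restate the sentence along these lines: *1000 participants allow for up to 26% loss; with 30% loss, 700 are evaluable.* This costs one sentence and no additional enrolment, and it can be done at once.

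A power figure for 700 should be added only after two things are reconciled: the design rates and test that produced 738, and the non-inferiority margin, which is -8.0% in the sample size section and 0.5% in the statistical analysis section. Until then, any single power figure would look more settled than the calculation behind it.
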